## 1. Brief layperson summary

One in four infants are born with low amounts of vitamin D stored in their body. This study is designed to test whether improving vitamin D status quickly after birth helps infants to build muscle and bone mass and to normalize growth. This is important since the investigators have noticed in previous work that infants with low vitamin D have higher body weight relative to body length later on and that those who develop very good stores quickly have a leaner body type. Therefore, in this study infants with low stores early after birth will be given either the regular amount of supplementation or a higher amount to more rapidly build up the vitamin stores in the body. Infants in both groups will be measured for muscle and fat mass and bone mineral content and density at standardized ages during the first year of life and into the toddler years. The information will inform health care professionals and parents of the importance of establishing good vitamin D stores early in life. Vitamin D supplementation is a modifiable factor that is already recommended for all term born infants. Knowing how much is needed in infants born with low stores has not been tested in a controlled manner in Canada.

## 2. Trial objectives

Primary Trial Objective: To test whether rapid correction of vitamin D status early in the neonatal period results in greater lean mass by 3 mo of age and sustained to 3 y. It is hypothesized that neonates with low vitamin D status and provided a vitamin D supplement of 400 IU/d will have lower accretion of lean mass by 3 mo of age and thereafter to 3 y compared to infants given 1000 IU/d.

Secondary Trial Objectives are designed *a priori* to test:

1) Whether correction of low vitamin D status early in infancy using 1000 IU/d of vitamin D normalizes body composition (lean, fat, bone mass) across infancy and to 3 y of age;

Tertiary Objective: outside of the trial, establish a healthy reference group with good neonatal vitamin D stores ( $>50$  nmol/L 25(OH)D) and given the AI of 400 IU vitamin D/d with all of the same measurements as the trial since these are not all available (e.g. IGF-1, IGFBP3 using same assays). The reference group will be frequency matched to trial infants based on skin color of the infants and season.

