### 3.5 What are the inclusion/exclusion criteria?

For **screening**, inclusion criteria is any healthy term born infant of appropriate weight for gestational age (AGA) based on a Canadian growth reference [1] and born to a generally healthy mother of any race. For the randomized trial, infants must have serum 25(OH)D <50 nmol/L; and for those in the reference group >50 nmol/L. For both the trial and reference groups other **inclusion criteria** are: born to mothers with otherwise healthy pregnancy free of medications that impact vitamin D metabolism (except vitamin/mineral supplements) or fetal growth and intent to breastfeed to at least 3 mo. For the trial we will not exclude on the basis of maternal pre-pregnancy BMI, but will document pregnancy weight gain and obstetrical history from the medical record. For the healthy reference group we will recruit from our screening pool only infants born to mothers of healthy weights (pre-pregnancy BMI 18.5-24.9 kg/m^2) and weight gain according to IOM criteria [2]. **Exclusion criteria** are maternal smoking in pregnancy as it limits growth; and diabetes, preeclampsia, celiac disease, inflammatory bowel disease etc. and medications that impact vitamin D/mineral metabolism. All maternal medications will be documented.

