### 3.11 What is the proposed sample size and what is the justification?

The minimum sample size (n=66) is based on the primary objective, lean mass in g at 3 mo of age and an effect size of 9% (400 g), SD of 670 g, an allocation ratio of 1:1, power of 80 and alpha of 0.01. Accounting for possible dropouts ( $\leq 10\%$ ) or missing data (1% due to movement artifact) we will study 74 infants/group. The attrition is based on 3 similar studies with an average attrition of 9% [3, 15, 16]. We have used a more stringent estimate based on an alpha of

1% to enable multiple comparisons over time and in the event of greater variability in lean mass. We believe the estimated effect size is clinically meaningful since infants in the preliminary healthy status group treated with 400 IU/d increased lean mass between 1 mo and 3 mo by 670 g and the  $\Delta$  400 g anticipated between our trial groups by 3 mo represents 60% of that normal change which would be enough to reset growth for a leaner body phenotype.

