### 3.16 What is the proposed type of analyses?

Intent-to-treat analyses. All data entry will be audited and baseline characteristics expressed as mean (SD) or median (IQR) depending on normality for continuous data or as proportions for ordinal data (e.g. white non-white, sex). Continuous data for primary outcome measurements will be expressed as mean (95% CI) or proportion (95%CI). All data analysis will be conducted using SAS (version 9.3, SAS Inst. and SAS University Edition). Continuous data for the primary outcome will be examined using mixed model ANOVA accounting for fixed effects (sex,

dosage, time, dosage\*time) and random effects (e.g. infant ID.) with post-hoc testing as applicable (i.e. 2 treatment groups and 1 reference group over 4 time-points) using Tukey-Kramer correction and significant differences accepted at  $p < 0.05$ . The mixed model ANOVA does not require that data be parametric nor of homogeneous variance. Data will be tested using Kolmogorov-Smirnov, Anderson-Darling, or a Shapiro-Wilk tests for normality and where necessary transformed (e.g. log value etc.) to meet the assumptions of the post-hoc tests. The mixed model uses all available data, missing data does not result in omission of an infant's existing data. If more than 5% of data is missing, imputation approaches will be considered. Compliance (unused product and surveyed data) will be compared between groups. For the secondary objectives, a MIXED model will be used for continuous data. The proportion of those achieving the 50 and 75 nmol/L targets will be expressed as a proportion (95% CI) and differences among groups tested using Chi-square analyses or other similar tests based on numbers in each cell or logistic regression. We are experienced in all of these tests [3, 15]. The healthy reference group will be statistically analyzed to form reference curves (e.g., lean mass) using LMS methods [18].

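### The secondary objective on normalizing body composition has no criterion for similarity, and its reference group differs from the trial arms by design on maternal weight

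*Protocol*

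**What the plan says.** Protocol section 2 lists, as a secondary objective to be tested a priori, whether correcting low status "using 1000 IU/d of vitamin D normalizes body composition (lean, fat, bone mass) across infancy and to 3 y of age". It gives no margin, normal range or named comparator. The healthy reference group appears under a tertiary objective in the same section and is frequency matched on skin color and season.

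Section 3.16 brings that group into the mixed model for the primary outcome, lean mass, with "post-hoc testing as applicable (i.e. 2 treatment groups and 1 reference group over 4 time-points) using Tukey-Kramer correction" and significance at p < 0.05. For the secondary objectives it names only a mixed model for continuous data. It also plans LMS reference curves from the reference group.

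Section 3.5 selects the two populations differently. "For the healthy reference group we will recruit from our screening pool only infants born to mothers of healthy weights", meaning pre-pregnancy BMI 18.5–24.9, with weight gain within the IOM criteria. By contrast, "For the trial we will not exclude on the basis of maternal pre-pregnancy BMI", and no weight-gain criterion is listed for the trial. The fixed effects in section 3.16 are sex, dosage, time and dosage by time, with no maternal term.

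**The concern.** To normalize is to bring a group to resemble a norm. The section on additional safety monitoring says that no standards exist for infant lean, fat and bone mass, so the reference group is the only norm the protocol sets up for these outcomes. A difference test against it can show that the 1000 IU/d arm is not normal. It cannot show that the arm is normal. Multiplicity correction makes this worse: the stricter the correction, the easier it is to find no significant difference.

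The second problem is comparability. The protocol treats maternal weight as relevant to a healthy norm, since it selects reference infants on it, and then neither matches on it nor lists it in the model. The objective could therefore be answered yes through imprecision, or answered either way through maternal weight. Neither answer would be about vitamin D.

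**Working it through.** **Inputs.** Section 3.11: "an effect size of 9% (400 g), SD of 670 g, an allocation ratio of 1:1, power of 80 and alpha of 0.01". The minimum is 66 per group, and "we will study 74 infants/group". Section 3.12: reference group of 74. Section 3.16: three groups, four time-points, p < 0.05. My assumptions: the SD of 670 g at 3 months also holds in the reference group, 66 to 74 infants per group are analyzed, model degrees of freedom are 200 to 600, and the normal approximation is adequate.

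**The plan's own figure.** n per group = 2 × (2.5758 + 0.8416)² × 670² / 400² = 65.5, rounded up to 66. This matches the protocol with a two-sided alpha of 0.01 (one-sided would give 57). Allowing 10% dropout, 66 / 0.90 = 73.3, rounded up to 74.

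**Precision.** SE = 670 × √(2/n), which is 116.6 g at 66 per group and 110.1 g at 74.

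**What the difference test can miss.** With critical value c, the interval half-width is c × SE, and a true deficit d is non-significant with probability Φ(c − d/SE); the opposite tail is negligible. For Tukey, c is the 95% studentized range quantile divided by √2. The protocol does not say how many comparisons the correction covers, so both readings are shown, with an uncorrected test for scale.

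| Correction | c | Half-width | Miss 400 g | Miss 300 g | Miss 200 g |
|---|---|---|---|---|---|
| None | 1.96 | 216–229 g | 5–7% | 22–27% | 56–60% |
| 3 groups at one visit | 2.35–2.36 | 259–275 g | 10–14% | 35–42% | 70–74% |
| All 12 group-by-time cells | 3.28–3.31 | 361–386 g | 36–45% | 71–77% | 93–94% |

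Example, 66 per group and 12 cells: Φ(3.307 − 400/116.6) = Φ(3.307 − 3.430) = Φ(−0.123) = 0.451.

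**What a margin-based criterion could do.** Equivalence is shown if the 90% CI lies within ±M. If the groups are truly equal, power = 2Φ(M/SE − 1.645) − 1:
- M = 400 g: 93% at 66 per group, 95% at 74.
- M = 300 g: 65% and 72%.
- M = 200 g: 6% and 14%.

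A 400 g margin is lenient. At 66 per group, a true 300 g deficit would still pass with probability Φ((400 − 1.645 × 116.6 − 300)/116.6) = Φ(−0.787), about 22%.

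**Restricted comparison.** The documents do not say how many trial mothers would meet the reference criteria. Assuming 40–50% of 66 (26 to 33 infants) against 66 reference infants:
- 33 infants: SE = 670 × √(1/33 + 1/66) = 142.8 g, giving about 75% power at a 400 g margin.
- 26 infants: SE = 670 × √(1/26 + 1/66) = 155.1 g, giving about 65%.

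**Comparability.** Setting sections 2, 3.5 and 3.16 side by side: selection differs on maternal BMI and weight gain, matching covers skin color and season, and the model adds only sex. Nothing listed removes the maternal difference. The documents do not allow the size or direction of the resulting bias to be estimated.

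**The case against.** Much can be said for the plan, and part of it stands.

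- A reader might infer that Tukey-Kramer is the only analysis of the whole objective. It is not. The sentence is written for lean mass; fat and bone get only a mixed model, and the LMS curves are a second use of the reference group. This stands, but neither supplies a criterion for similarity.
- A reader might infer that the sponsor will call a non-significant difference normal. No section says so. The difficulty is that the protocol offers no other rule.
- A reader might take the upper figure, about 45%, as the chance of missing a 400 g deficit. That assumes the 12-cell correction and 66 per group. The post-hoc tests are to be used as applicable, and with three groups at one visit the figure is 10–14%.
- The objective names no comparator, and the randomized contrast answers part of it. True, but that contrast shows whether 1000 IU/d differs from 400 IU/d, not whether either reaches a norm.
- Restricting the reference group to healthy-weight mothers is deliberate and disclosed, and is a sensible way to define a norm. It does not make a gap attributable to vitamin D.
- A margin and covariates could be set in a statistical analysis plan, which is not at hand. That would be a good place for the remedy. The point here is that the protocol itself pairs a similarity objective with a difference test and a differently selected comparator.

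**Conclusion.** The point holds for the secondary objective. As written, the comparison with the reference group cannot establish normalization, and any gap it shows cannot be attributed to vitamin D status alone. For lean mass at 3 months, a true deficit of 400 g, the amount section 3.11 calls clinically meaningful, is missed in about 10–14% to 36–45% of trials depending on the comparisons Tukey covers, and a 300 g deficit in about 35–77%. These figures rest on the 670 g SD applying to the reference group and on 66 to 74 infants per group. The documents give no SD or meaningful difference for fat, bone or later ages, so no such figures can be given there.

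A reader might conclude that the trial's main comparison is compromised. The documents do not support that: the randomized 1000 versus 400 IU/d contrast is not confounded by how the reference group was selected, and its sample size reproduces.

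**What to change.** 1. State that normalization will not be inferred from a non-significant difference. Report the 1000 IU/d minus reference difference with its confidence interval, or express trial infants as z-scores from the LMS curves, which also cover fat, bone and later ages. Judge the result against a pre-specified margin. For lean mass at 3 months it should be no wider than the trial's own 400 g, and the sponsor should justify a tighter one, given the power shown above. The other outcomes and ages need their own margins, for example on the z-score scale.
2. Repeat the reference comparison adjusted for maternal pre-pregnancy BMI and weight gain, or restricted to trial infants whose mothers meet the reference criteria. Section 3.5 already has pregnancy weight gain and obstetrical history documented; confirm that pre-pregnancy BMI is captured for trial mothers too.
3. Rest causal statements on the randomized contrast and describe the reference comparison as non-randomized.

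The cost is wording and one or two further analyses, with no extra infants at a 400 g margin. The downside is that normalization becomes harder to claim, and the restricted set is smaller and less precise.

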## 3. Proposed trial

### 3.1 What is the proposed trial design?

Double blinded randomized parallel group trial.

### 3.2 The planned trial interventions?

Standard of care 400 IU vs. 1000 IU vitamin D/d from baseline (1 wk) to 12 mo in neonates with low vitamin D status; and a reference group given 400 IU vitamin D/d.

### 3.3 Practical arrangements for allocation?

We will use RANDOMIZE.net according to variable block sizes and stratification, 2 treatment arms and verification of entry criteria. Stratification will be on measured skin color of the infant (**Diagram 1**). We will track the reference group using this system.

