### 3.15 How many centers will be involved?

One research centre with recruitment from 1 hospital that we work with; recruitment site will be documented for each infant and considered in the analyses.

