### 3.17 Are there any planned subgroup analyses?

For the primary objective we do not have subgroup analyses planned, but have considered possibilities. In the event that infant sex is not balanced we will use sex as a covariate. The potential subgroup analyses we have identified are measured skin color (pigmentation). These would only be explored in efforts to generate hypotheses and consequently to design future studies. Skin pigmentation is embedded in the design as infant skin color will be used as stratification criteria. Our objective measures of pigmentation could improve understanding the biological response to vitamin D.

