| July-October 2015  | 
 
Funding notice (July)
 
Steering committee meeting (July)
 
Ethics review (Aug)
 
Students begin program (Sept)
 
Register trial www.clinicaltrials.gov
 
Set up RANDOMIZATION.net
 
Printing of study materials
 
Prepare/receive supplements
 
 | 
All staff are currently available to transfer from other projects.
 
Letter of no objection from Health Canada will be obtained.
 
Euro-Pharm has agreed to provide supplements in kind – see budget page attachments for letter of support.
                                                                                                                                                                                                                                                                                                                                                                                                                                                                                      |
| October 2015-2018  | 
Begin screening recruitment at each hospital's newborn unit (Ethics review in Quebec hospitals is now streamlined so we apply to one site and the others adopt the certificate):
 
 
Ste. Justine Hospital
 
Lakeshore General Hospital
 
McGill University Health Centre (new 2015 Glen site)
 
                      | 
Recruitment is to be overseen by [name]. Study staff and trainees will visit each hospital 5 d a week to recruit for screening. Parent(s) of healthy newborn infants born to generally healthy mothers will be asked if they would like vitamin D status measured as screening for a trial; and if so this would be done using blood taken at the same time as newborn screening. Short demographic and obstetric surveys would be completed. Vitamin D will be measured daily and parents contacted to see if they would like to participate in the trial depending on vitamin D status below 50 nmol/L 25(OH)D or above (reference group). Results of the screening will be given to parents; not thereafter unless safety issues arise.
 |

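### The primary model leaves out the skin-colour factor used to stratify randomisation, and the protocol gives two incompatible rules for including sex

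*Protocol*

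**What the plan says.** **Stratification.** Protocol section 3.3: "Stratification will be on measured skin color of the infant". The subgroup section (the second of two numbered 3.17) repeats it: "Skin pigmentation is embedded in the design as infant skin color will be used as stratification criteria". The only analytic role given to skin colour is as a possible hypothesis-generating subgroup.

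**Primary model.** Section 3.16: "Continuous data for the primary outcome will be examined using mixed model ANOVA accounting for fixed effects". The list in brackets is sex, dosage, time and dosage by time. Random effects are given by example only, namely infant ID. Post-hoc comparisons cover the two randomised arms and the non-randomised reference group over four time-points.

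**Sex.** Section 3.16 lists it without condition. The subgroup section, in a paragraph that opens with the primary objective, says: "In the event that infant sex is not balanced we will use sex as a covariate".

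**Site.** Section 3.15: "One research centre with recruitment from 1 hospital that we work with; recruitment site will be documented for each infant and considered in the analyses". Section 3.12 names three recruiting hospitals. Table 2 has the entry "Begin screening recruitment at each hospital's newborn unit" followed by three hospital names. Section 3.16 has no site term.

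**The concern.** When randomisation is balanced within strata of a factor that predicts the outcome, the treatment difference varies less from trial to trial than a model without that factor assumes. The reported standard error is then too large, the test rejects less often than its nominal level, and some power is lost. The protocol builds skin colour into the design and then gives it no place in the primary model.

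The two statements on sex are a separate fault. Sex is not a stratification factor, so some chance imbalance is to be expected. A rule that admits sex only after looking at the balance, with no definition of imbalance, lets observed baseline data choose the covariate set. If sex is judged balanced, section 3.16 gives one primary p value and the subgroup section another.

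The hospital count matters because it decides whether there is any site effect to consider.

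**Working it through.** **1. The plan's own sample size.** Inputs from section 3.11: difference 400 g, SD 670 g, alpha 0.01, power 80%, allocation 1:1. Sidedness is not stated; two-sided reproduces the figure.

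n per group = 2 × (2.576 + 0.842)² × (670/400)² = 2 × 11.68 × 2.806 ≈ 65.5, so 66. This matches. Dropout: 66/0.90/0.99 = 74.07, in line with the stated 74. No stratum or covariate term enters this calculation.

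**2. Assumption.** Let R² be the share of lean-mass variance explained by skin colour. The protocol gives no value, so 2, 5 and 10% are assumed, with 0 as the no-effect case. The check treats the 3-month endpoint as a plain two-arm comparison with perfect balance within strata. It is not the full repeated-measures model.

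**3. Formulas.** Under stratified balance the true standard error is √(1−R²) times the one that the unadjusted model reports.

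- Overstatement of the standard error: 1/√(1−R²) − 1
- Actual size of the unadjusted test at nominal 5%: 2 × [1 − Φ(1.96/√(1−R²))]
- Standardised effect with no adjustment: 400/(670 × √(2/66)) = 400/116.6 = 3.430
- Power without the term, two-sided alpha 0.01: Φ((3.430 − 2.576)/√(1−R²))
- Power with the term: Φ(3.430/√(1−R²) − 2.576)

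| Assumed R² | SE overstated | Size at nominal 5% | Power without term | Power with term | Gain (points) |
|---|---|---|---|---|---|
| 0 | 0 | 5.0% | 80.3% | 80.3% | 0 |
| 2% | 1.0% | 4.8% | 80.6% | 81.3% | 0.7 |
| 5% | 2.6% | 4.4% | 81.0% | 82.7% | 1.8 |
| 10% | 5.4% | 3.9% | 81.6% | 85.1% | 3.5 |

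Gains are taken before rounding. Alpha 0.05 is the threshold in section 3.16; alpha 0.01 is the planning value in section 3.11.

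**4. Check by simulation.** With 20,000 simulated trials, 66 per arm and two equal strata, power at alpha 0.01 without and with the term was 79.20 and 80.13% (R² 2%), 79.64 and 81.58% (5%), and 79.88 and 83.43% (10%). The gains are 0.93, 1.94 and 3.55 points, in line with the table. The levels are slightly lower because the simulation uses the t distribution.

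**5. The two sex rules side by side.**

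| Observed sex balance | Section 3.16 | Subgroup section |
|---|---|---|
| Judged unbalanced | sex in model | sex in model |
| Judged balanced | sex in model | sex not in model |

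They conflict only in the second row, but which row applies is unknown until the data are seen, and no criterion separates the rows.

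**6. Hospitals.** Section 3.15 gives one; section 3.12 and Table 2 each name three. With one hospital, the undertaking in section 3.15 to consider site has nothing to act on.

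**The case against.** The strongest reply is that the omission is harmless in direction and small in size. That stands: there is no bias, no inflated error, and no cost at all if skin colour is unrelated to lean mass.

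A reader might infer three stronger things that the documents do not support.

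- *That leaving out the factor wastes the stratification.* It does not. The arms are still balanced and the estimate is still more precise; only the reported standard error is too large.
- *That the term lifts power from 80% to 81–85%.* This compares against the wrong baseline. Stratified balance also raises the power of the unadjusted test, to 80.6–81.6%, so the gain is 0.7 to 3.5 points.
- *That section 3.15 promises a site term which section 3.16 then breaks.* Section 3.15 says only that site will be considered, and the random effects in section 3.16 are open-ended. Details of site handling may properly sit in an analysis plan. What stands is the contradiction in the hospital count.

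On sex, it can fairly be said that the trigger is a baseline characteristic rather than the outcome, that analysis is planned on blinded groups, and that the two rules agree when sex is unbalanced. This limits the scope for abuse but does not make the two statements compatible.

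The strata themselves are not visible, because Diagram 1 is not shown. White versus non-white is an inference from sections 3.9 and 3.12.

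**Conclusion.** The point holds in a modest form. The fixed effects in section 3.16 are a written-out list that omits the stratification factor, and the rule for sex contradicts itself within the protocol. Neither is merely deferred to an analysis plan, because the protocol states both. The sex contradiction is the more important part, since it leaves the primary model undetermined until baseline data are seen.

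The stratification omission costs efficiency, not validity. For an assumed R² of 2 to 10%, size is 4.8 to 3.9% at nominal 5%, and 0.7 to 3.5 points of power are forgone at 66 per group and alpha 0.01. These figures rest wholly on the assumed R² and on a single two-arm comparison at 3 months. The hospital count is a factual inconsistency to be reconciled.

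**What to change.** - In section 3.16, add the skin-colour category used for stratification as a fixed effect. Reference infants were never randomised and so have no randomised stratum; use the same measured category for them.
- Keep sex as an unconditional, prespecified fixed effect, and delete the sentence in the subgroup section that makes it depend on imbalance.
- Reconcile sections 3.12 and 3.15 and Table 2 on the number of recruiting hospitals. If there is more than one, state how site enters the analysis; if only one, remove the undertaking to consider it.
- Do not add baseline lean mass as a covariate while baseline is also a modelled response. The four time-points in section 3.16 appear to be baseline, 3, 6 and 12 months (section 3.7).

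The cost is wording, about 1 degree of freedom for skin colour if it has two categories, none for sex (already in the section 3.16 model), and up to 2 more if three sites enter as fixed effects. The sample size does not change.
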